### Process evaluation

The process evaluation will aim to identify and explain all mechanisms and processes (ie, the intervention theory) that enabled or acted as a barrier to the implementation of the enhanced rehabilitation intervention. The process evaluation will help build a picture of how the intervention was carried out in reality and what factors shaped it. By carrying out a process evaluation, it will be possible to identify if observed impacts are solely due to the enhanced rehabilitation programme, or if these impacts are a result of a number of external and internal variables that are closely linked to the environment and the context in which the intervention takes place.^48–51^

The specific objectives will be to:

Refine the programme theory from the previous realist review that was used to develop the intervention.^21^ This programme theory will explain how the researchers envisage the intervention to work, to reach its expected outcomes.Investigate therapists’ expectations and experience of implementation, their previous experience and training and their learning throughout the conduct of the trial.Investigate the mechanisms driving and shaping the tailoring of the enhanced rehabilitation intervention to individual patients.Investigate trial participants’ (patients and carers) experiences and views about their involvement in the trial as well as their experience of care in either arm of the trial.Map and synthesise all data collected in order to test the refined programme theory and explain the trial findings.

#### Process evaluation data collection

Semistructured telephone interviews will be conducted with:

A purposive sample of 60 patient participants in each of the two trial arms and up to 30 of their carers. Patients will be purposively sampled to ensure diversity based on age, functional impairment (using baseline NEADL scores) and the presence or absence of a family carer. Interviews will take place after the 17-week assessment and will be audio recorded.The therapists delivering the enhanced rehabilitation programme, which will explore implementation from the therapists’ perspectives. Interviews will be conducted midway through their involvement in the trial, and at the end, in order to investigate learning over time.

#### Data on intervention delivery and adherence

Therapists will record key reflections on ‘critical incident reports’.The visiting therapist will record the length and content of each extra rehabilitation therapy session on a case report form.All patient participants will be given a therapy session record, where visiting therapists will record the number, length and content of usual rehabilitation care. Whenever possible, routinely collected electronic data that therapists complete on their Therapy Manager system, or its equivalent, will be collected.An online questionnaire will be emailed to participating therapists in order to capture therapists’ relevant training, previous experience and familiarity with the trial intervention.

Qualitative data will be analysed following a thematic analysis approach^52^ that will be guided by the proposed programme theory. Quantitative data (record forms and online questionnaires) will be analysed using descriptive statistics, which will allow the exploration of frequency of responses. All data sets will be synthesised in order to describe the complex nature of the enhanced rehabilitation intervention.

### Patient and public involvement

There has been patient and public involvement (PPI) at all stages including refining the research question, choosing outcomes relevant to patients, commenting on the burden of the intervention and of trial participation. A PPI coinvestigator will continue to contribute to the trial management group, including comments on patient-facing materials and the dissemination plan.

### Ethics and dissemination

NHS research ethics approval was obtained from North East—Tyne & Wear South Research Ethics Committee, reference 18/NE/0300. The current protocol is V.4.0 (11 December 2019). A Trial Steering Committee is providing overall supervision and an Independent Data Safety and Monitoring Committee is responsible for reviewing and assessing recruitment, interim monitoring of safety and effectiveness, trial conduct and external data.

All safety events will be recorded by researchers when they are made aware of the event by the patient, carer, the treating clinicians or therapists. Adverse event reports and serious adverse events (SAEs) not related to the intervention will be entered on to the remote data entry system. Each SAE will be assessed by the relevant principal investigator (PI) to determine whether it is related to the intervention. A related SAE will be assessed by the CI to determine whether it is expected. If the SAE is related and unexpected, it will be reported to the Research Ethics Committee and sponsor in an expedited manner.

Reporting of the trial will be consistent with the Consolidated Standards of Reporting Trials 2010 Statement (patient-reported outcomes and non-pharmacological interventions).^53^ We will submit the final report to a peer-reviewed academic journal, according to our publication strategy and authorship policy. Research data will be available for secondary analysis on reasonable request.

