### Secondary objectives

To compare the cost-effectiveness of an enhanced rehabilitation programme following surgical repair of proximal femoral fracture in older people compared with usual care at 52 weeks follow-up.To determine the effectiveness of an enhanced rehabilitation programme following surgical repair of proximal femoral fracture in older people compared with usual care, in terms of the performance of activities of daily living at 17 weeks follow-up.To determine the effectiveness of an enhanced rehabilitation package following surgical repair of proximal femoral fracture in older people compared with usual care, in terms of anxiety and depression at 17 and 52 weeks follow-up.To assess whether the enhanced rehabilitation intervention creates change in self-efficacy, hip pain, cognitive function, fear of falling and physical function as potential mediators for improving activities of daily living at 17 and 52 weeks follow-up.To assess whether the enhanced rehabilitation intervention creates change in strain, anxiety and depression in carers at 17 and 52 weeks follow-up.To determine the mechanisms and processes that explain the implementation and impacts of the enhanced rehabilitation programme and whether there are adverse effects.

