#### Usual rehabilitation care

Usual care consists of a multidisciplinary rehabilitation delivered by the acute hospital, community hospital and community services depending on patients’ individual needs at different times during their recovery and on the availability and accessibility of services in different areas. The multidisciplinary team delivering care and rehabilitation may include: orthopaedic surgeons, orthogeriatricians, nurses, physiotherapists, occupational therapists, dieticians, pharmacists, general practitioners (GPs) and social workers. The settings for care include acute orthopaedic or orthogeriatric wards, rehabilitation units in community hospitals, rehabilitation beds in care homes, the patient’s own home and care home settings, all delivered by a variety of community teams in both health and social care services. There will be no restrictions on concomitant medications or treatments.

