#### Enhanced rehabilitation

The main aim of the intervention is to enhance usual rehabilitation by increasing patients’ self-efficacy^25^ and increasing the amount and quality of patients’ practice of physical exercise and activities of daily living to improve functional outcomes at follow-up. Self-efficacy will be enhanced by means of a patient-held information workbook and a goal setting diary. The workbook will include:

Information about what has happened to them and what to expect from their recovery.Information about NHS, council and voluntary sector services including falls’ prevention programmes.How to manage their recovery, set goals and monitor progress of their rehabilitation; reduce fear of falling.

In addition to whatever community-based rehabilitation is provided as part of usual care, we will provide up to six additional therapy sessions, once patients are discharged home. These can be delivered by physiotherapists, occupational therapists or their assistants, who have been trained to deliver these extra sessions alongside the workbook, using the diary to set goals and monitor progress. The therapists will tailor these extra sessions, so that the total number of sessions used, the time scale for their delivery and the sessions’ content will vary between patients according to need but may include the practice of specific exercises and activities of daily living. Throughout the running of this trial, therapists will receive on-going support via emails, newsletters and refresher events.

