**Carer completed measure—secondary outcome**		
Caregiver Strain Index^42^	13 items in the domains: employment, financial, physical, social and time. Positive responses to seven or more items indicate a greater level of strain	(0–13)
HADS^28^	Anxiety and depression in carers. Two subscales (0–21) with higher score indicate greater anxiety or depression	(0–21)

**Table 2 T2:** Fracturein the Elderly Multidisciplinary Rehabilitation—phase III (FEMuR III) protocol schedule of forms and procedures

Procedures	Screening	Baseline/randomisation*	Trial intervention†	17 weeks postrandomisation follow-up	Qualitative interviews	52 weeks postrandomisation follow-up
Eligibility screening and consent						
Assessment of eligibility criteria	X					
Written and informed consent (patient/carer)	X					
Confirm consent		X	X	X	X	X
Randomisation		X				
Discharge data		X				
Outcome measurement— patient						
Nottingham Extended Activities of Daily Living		X		X		X
Hospital Anxiety and Depression Scale (HADS)		X		X		X
Abbreviated Mental Test Score		X		X		X
Visual Analogue Scale (VAS) hip pain intensity		X		X		X
Falls Efficacy Scale—International		X		X		X
Visual Analogue Score—Fear of Falling		X		X		X
EuroQol-5D-3L		X		X		X
Client Service Receipt Inventory		X		X		X
Grip strength		X		X		X
Short Physical Performance Battery				X		X
Outcome measurement— carer						
Caregiver Strain Index		X		X		X
HADS		X		X		X
Trial intervention†			X			
Qualitative interviews						
Re-affirm consent verbally specifically for qualitative phone interview. (patient/carer)					X	
Qualitative telephone interview					X	
Safety event reporting						
Monitoring of adverse events			X	X	X	X
Monitoring of serious adverse events			X	X	X	X

Participant follow-up visits should take place at 17 (±2 weeks) and 52 (±2 weeks) weeks postrandomisation.

*Randomisation and baseline should take place no later than 6 weeks after hip fracture repair surgery.

†If randomised to intervention arm.

The research assistant will assess patient participants’ cognitive function at baseline, 17 and 52 weeks using the Abbreviated Mental Test Score.^35^ The research assistant will measure physical function at baseline, 17 and 52 weeks using the grip strength test^36–38^ and using the Short Physical Performance Battery^39 40^ at 17 and 52 weeks.

Carer participants will complete the Caregiver Strain Index^41^ and the HADS^28^ at baseline, 17 and 52 weeks.

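### The schedule ties adverse event monitoring between randomisation and week 17 to the intervention arm only, leaving any between-arm comparison of harms open to unequal ascertainment

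*Protocol article*

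**What the plan says.** Four parts of the protocol article bear on this.

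- **Table 2 (schedule of forms and procedures).** The row reads "Monitoring of adverse events X X X X". The four ticks fall under the trial intervention column, the 17-week follow-up, the qualitative interviews and the 52-week follow-up. The SAE row is ticked identically. The heading of the first of these columns carries a dagger, explained below the table as "If randomised to intervention arm". The common visits are also fixed there: "Participant follow-up visits should take place at 17 (±2 weeks) and 52 (±2 weeks) weeks postrandomisation".
- **Ethics and dissemination.** The recording rule is "All safety events will be recorded by researchers when they are made aware of the event by the patient, carer, the treating clinicians or therapists". It is not limited by arm or by period. The same section makes the data monitoring committee responsible for interim monitoring of safety.
- **Enhanced rehabilitation.** In addition to usual care, "we will provide up to six additional therapy sessions, once patients are discharged home". The section on intervention delivery and adherence has the visiting therapist complete a case report form for each extra session.
- **Secondary objectives.** The last one is to "explain the implementation and impacts of the enhanced rehabilitation programme and whether there are adverse effects", after first naming mechanisms and processes.

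**The concern.** Table 2 and the recording rule do not describe the same procedure. The rule covers every safety event in the trial. The schedule places the only monitoring slot between randomisation and week 17 in a column that controls do not have.

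The contact pattern points the same way. Events enter the record when somebody tells a researcher, and the intervention arm has more occasions on which an event can come to light: extra sessions with therapists who are trained for the trial and already fill in a trial form at each visit. A fall at home in week 8 could be known through such a session in one arm, yet depend on recall at week 17 in the other.

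At stake is the objective on adverse effects. Risk and benefits names injury or falling during therapeutic exercise as the possible harm. Falls and minor injuries are also the events most easily missed between visits. Extra recording could look like harm, or make a real excess hard to interpret. The committee's interim safety review would rest on the same records. An analysis plan cannot recover control-arm events that were never elicited.

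**Working it through.** **1. Chances for an event to be recorded, by arm**

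| Route | Control | Intervention | Source |
|---|---|---|---|
| Scheduled monitoring, randomisation to week 17 | None, read literally | Yes | Table 2 and dagger footnote |
| Monitoring at 17 and 52 weeks | Yes | Yes | Table 2 |
| Qualitative interviews | 60 patients | 60 patients | Table 2; Process evaluation data collection |
| Usual-care clinicians and therapists | Yes | Yes | Usual rehabilitation care |
| Additional trial therapy sessions | 0 | Up to 6 | Enhanced rehabilitation |

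Three of the five routes are common to both arms. The two that differ both favour recording in the intervention arm.

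**2. Arm size for the illustration**

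Inputs from Sample size calculation: difference 2.4, SD 10, R² 0.52, alpha 5% (taken as two-sided), power 90%, retention 79%.

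- Residual SD = 10 × √(1 − 0.52) = 6.93.
- This gives 176 per arm, or 352 completers, as stated.
- 352 / 0.79 = 446 recruited, as stated.
- At 1:1 allocation, 446 / 2 = 223 per arm.

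These figures reproduce and are not in dispute.

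**3. Illustration of unequal capture, with no true harm**

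The document gives no event risk and no capture probability, so both are assumed. Let p be the true risk of at least one event, the same in both arms, and let c₀ and c₁ be the probabilities that such a patient is recorded in control and intervention.

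- Recorded risks are p·c₀ and p·c₁.
- Recorded risk ratio = c₁ / c₀, whatever p is.
- Chance of a two-sided p<0.05 = Φ[(p·c₁ − p·c₀ − 1.96·SE₀) / SE₁], with SE₀ the pooled and SE₁ the unpooled standard error of a difference in proportions at 223 per arm.

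| c₀ (control) | c₁ (intervention) | Recorded risk ratio | p = 20% | p = 30% | p = 50% |
|---|---|---|---|---|---|
| 0.70 | 0.70 | 1.00 | 5% | 5% | 5% |
| 0.80 | 0.90 | 1.12 | 8% | 11% | 19% |
| 0.70 | 0.80 | 1.14 | 9% | 11% | 19% |
| 0.70 | 0.90 | 1.29 | 21% | 32% | 58% |
| 0.60 | 0.90 | 1.50 | 43% | 62% | 91% |

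The last three columns give the chance of a spurious significant difference. Example: p = 30% with capture 0.70 v 0.90 gives recorded risks of 21% and 27%, or about 47 v 60 patients of 223. The ratio is 0.27 / 0.21 = 1.29, and the chance is 32%.

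With a 10-point capture gap that chance stays between 8% and 19%; only the wider gaps push it well above. All 223 per arm are treated as fully followed, although the plan expects 79% retention.

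**The case against.** The case against is substantial, and most of it limits the claim.

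- **The recording rule is neutral between arms.** It covers all safety events, and its list of informants is not confined to trial therapists. Usual care may involve "orthopaedic surgeons, orthogeriatricians, nurses, physiotherapists, occupational therapists, dieticians, pharmacists, general practitioners (GPs) and social workers", any of whom could report an event in a control patient. This stands. The rule alone shows no asymmetry; Table 2 and its footnote do.
- **Both arms already have monitoring at 17 and 52 weeks, and the interviews sample the arms equally.** This stands too, so control events can still be captured. But the common routes add equally to both arms and do not offset the extra sessions.
- **The dagger may only mark who receives the programme.** It also sits on the trial intervention row, and the column is the table's only slot between baseline and week 17. That may be what was meant, but the table as printed says otherwise, and sites follow a schedule as printed.
- **No between-arm test of adverse events is stated.** Correct. The objective on adverse effects sits within the process evaluation aim, and tabulation may be left to the full protocol or analysis plan, so its absence is no fault here. The point concerns how the data are collected, which this document does fix.

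A reader might infer that the harms comparison *is* biased, that controls go unmonitored until week 17, or that events reach researchers mainly through the therapists delivering the programme. The document supports none of these. It shows more opportunity for recording in one arm, not how often that opportunity produces an additional record.

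**Conclusion.** The point holds as an inconsistency in planned data collection that leaves any comparison of harms between arms open to unequal ascertainment. The likely direction is more recorded events in the intervention arm, chiefly falls and minor injuries.

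The size is unknown. The ratios of 1.12 to 1.50 rest entirely on assumed capture gaps of 10 to 30 points and equal true risk, and must not be read as an estimate for this trial. How far the schedule affects practice also depends on whether sites apply Table 2 literally and on how the forms elicit events, neither of which the article shows.

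The primary outcome and the sample size are unaffected. The change is worth making because a stated objective and the interim safety review both depend on these records, and it must be made in collection rather than in analysis.

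**What to change.** 1. Reconcile Table 2 with Ethics and dissemination: state that AE and SAE monitoring runs from randomisation to week 52 in both arms, and remove the dagger's restriction from those two rows.
2. At the existing 17- and 52-week visits, put the same structured enquiry (falls, injuries, admissions, other events) to both arms, covering the interval since the last contact.
3. Record the source of every report.
4. Base the main between-arm comparison on events elicited in the same way in both arms. Also report all events from any source by arm, identifying those known only through trial therapy sessions.

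Therapist-reported events should not be dropped. The interval between the common visits is 52 − 17 = 35 weeks, and relying on recall alone in older patients could under-count the exercise-related falls that matter most. Showing both tables covers this.

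The cost is a small case report form and wording change at visits that already take place. The downside is that some events forgotten by the visit will appear only in the all-source table. When the article was submitted, 96 of 446 patients had been recruited and recruitment was suspended, so (446 − 96) / 446 = 78% of the planned sample could still have been covered from randomisation.

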### Trial status

At the time of submission, this trial had been open in nine sites and had recruited 96 patients and 10 carers, with a recruitment rate of two patient participants per site per month and a retention rate of 83%, which fulfilled the progression criteria of the internal pilot. However, recruitment to the trial is currently suspended because of the COVID-19 pandemic. Wherever possible, participants already recruited into the trial will complete their follow-up assessments over the telephone or by post, extra rehabilitation sessions will be delivered over the telephone. When trial recruitment resumes, updated recruitment information will be found on the website http://femur3study.co.uk/
